### 4.2. Why is this research important in terms of improving the health and/or wellbeing of the public and/or to patients and health care services?

Detailed profiling of cognitive Covid is a necessary first step before development and implementation of rehabilitation programmes targeting those cognitive domains found to be preferentially affected. Given the likely heterogeneity within the cognitive phenotype, to deliver maximum benefit to individuals the rehabilitation will be structured in modular fashion. The core programme will focus on those cognitive domains found to be most commonly and severely affected, around which optional add-on programmes will address other cognitive impairments found in this study to contribute to the functional impairments associated with cognitive Covid.

This work will lead to several important improvements in care. First of all, profiling of cognitive Covid will assist future diagnosis of this condition, particularly in terms of differentiating it from other cognitive disorders including those caused by neurodegenerative disease. Second, determination of the interaction between cognitive impairment and potentially modifiable aspects of long Covid, such as sleep disruption and anxiety, will identify those aspects of cognitive function which can be improved with therapeutic interventions targeting these modifying factors. Third, the provision of neuropsychological rehabilitation strategies will deliver better clinical outcomes for patients while health services

280 will additionally gain from provision of treatment plans suitable for widespread  
281 implementation.

282

283 **4.3 Review of existing evidence – How does the existing literature support this**  
284 **proposal?**

285

286 Long Covid is a new condition and as such there is no prior information concerning the  
287 nature of cognitive impairment within the disorder, its underlying biological basis or potential  
288 treatability. However, there is considerable evidence to support the hypothesis that cognitive  
289 dysfunction is a major component of long Covid and that this may respond to  
290 neuropsychological rehabilitation, resulting in improved functional outcomes.

291

292 4.3.1 Cognitive impairment after acute CV19 infection

293 Given the relative recency of the CV19 pandemic, the majority of available data on cognitive  
294 impairment post-infection relates to cases observed during and shortly after acute infection.  
295 A meta-analysis of over 3,500 cases of coronavirus infections (SARS, MERS and CV19)  
296 showed that cognitive impairment was present in a third of cases during admission, with  
297 33% of CV19 cases having executive dysfunction at discharge. Ongoing cognitive  
298 impairment beyond the acute stage is underlined by another study showing persisting  
299 cognitive dysfunction in over 75% of cases with mild-moderate acute disease. Work to date  
300 indicates that the cognitive domains primarily affected are episodic memory, attention and  
301 executive function with the cognitive impairment being independent of age, gender and  
302 prior medical conditions.

303 The notion that cognitive Covid is a major and distinct aspect of long Covid is reinforced by  
304 observations that the occurrence of cognitive impairment is unrelated to prior ITU admission  
305 and is not associated with fatigue, depression or severity of acute inflammation. Such  
306 data indicate that cognitive impairment occurs even after milder infections, independent of  
307 comorbidities or stress reactions. The potential negative impact on working age individuals,  
308 and in turn personal and national economies, is underscored by a UK study showing that  
309 dementia-like cognitive impairment was found in 26% of affected individuals, half of whom  
310 were working age.

311

312 4.3.2 Vulnerability of the central nervous system (CNS) to CV19

313

314 The prevailing hypothesis is that the vulnerability of certain physiological systems to SARS-  
315 CoV-2 relates to expression of the ACE2 receptor on cell surfaces, onto which viral proteins  
316 bind and obtain cellular entry. In the CNS the ACE2 receptor is highly expressed in neurons,  
317 astrocytes, oligodendrocytes and endothelial cells. Regionally, high ACE2 receptor  
318 concentrations are found in the olfactory bulb, substantia nigra, middle temporal gyrus, and

posterior cingulate gyrus. Recent work has confirmed the ability of SARS-CoV-2 to invade the brain from the periphery, with entry via the olfactory neural-mucosa interface. This provides the means by which SARS-CoV-2 can infiltrate brain regions receiving direct projects from the olfactory bulb, including the hippocampus and other medial temporal lobe regions. Given the role of these regions in memory, the widely reported memory impairment in cognitive Covid may relate in part to direct viral infection of these regions.

#### 4.3.3. Evidence of efficacy of cognitive rehab in other disorders

While there is a lack of any evidence base on the use of neuropsychological rehabilitation in individuals affected by the previous coronaviruses such as SARS, there is extensive experience in managing the cognitive sequelae of other brain infection disorders such as HIV and infectious encephalitis. This in turn builds on more than 40 years of research and clinical practice on cognitive rehabilitation in people affected by neurological conditions.

Restorative (e.g., retraining) or compensatory (e.g., strategies to adapt to memory impairment) are helpful in managing deficits in memory, attention and executive function arising from a wide range of neurological aetiologies. Currently, rehabilitation therapists can resort to a wide range of tools, strategies and aids to treat cognitive impairment. In a systematic review of cognitive rehabilitation for infectious encephalitis, 5/9 studies showed positive changes in memory. Cognitive training and rehabilitation can also lead to gains in executive function and memory in people with cognitive deficits secondary to HIV, and these gains are maintained over time. Studies of other neurological disorders also show benefits of training, with improved executive function in patients with multiple sclerosis who undertake therapeutic training.

In summary, work undertaken in patients with aetiologies and cognitive deficits similar to those described in cognitive Covid shows benefit from cognitive rehabilitation therapies. This informs the rationale for the current study.

## 5 Experimental design and methods

### 5.1 Plan of investigation

#### 5.1.1 Participant recruitment

[figure not shown]

Figure 1. Trial flowchart including sample size

## Workstream 1

80 participants will be recruited from three clinical sites, namely the Cognitive Disorders Clinic, University Hospitals Sussex NHS Trust (PI [name]), representing one of the first clinics nationwide to offer a dedicated diagnostic and therapeutic service for cognitive Covid, Southampton General Hospital (PI [name]), and Greater Manchester Mental Health NHS Foundation Trust (PI [name]). As part of a substudy, 100 participants (60-70 with long Covid and 30-40 controls) will undergo MRI scanning at the University of Sussex.

Participants will be offered reimbursement of up to £20 for each study visit.

## Workstream 2

For the RCT 120 participants (for justification of this sample size, see power calculation below) will be recruited from the same clinics. If eligible participants in WS1 can take part in WS2.

### 5.2.1 Work Stream 1: Phenotyping Cognitive Covid

Baseline demographic information will include: age, gender identity, sexual orientation, registered sex at birth, medical and drug history, ethnicity, years of formal education, socio-economic status, disability, and language. We will also acquire information on i) temporal relationship between acute CV19 symptoms and onset of cognitive problems, ii) temporal relationship between onset of other long Covid symptoms and onset of cognitive problems, iii) CV19 vaccination history and reported effect of vaccine (if any) on cognition.

Participants will complete several questionnaires including:

- Quality of life (EQ-5D-5L)

Cognitive Impairment in Long Covid: Phenotyping and Rehabilitation (CICERO) EDGE 143067; IRAS 302920; Protocol v1.13; 20/12/2024 16/39

- 380 • Life Space Assessment
- 381 • Social Functioning (SF-DEM)
- 382 • Instrumental Activities of Daily Living (IADL) Scale
- 383 • Generalised Anxiety Disorder Assessment (GAD-7)
- 384 • Patient Health Questionnaire (PHQ-8)
- 385 • Chalder Fatigue Scale
- 386 • Pittsburgh Sleep Quality (PSQI)
- 387 • DePaul Symptom Questionnaire – Post-Exertional Malaise (DSQ-PEM).

388 Cognitive function will be assessed using three complementary assessments (expanded  
389 below), to maximise understanding of cognitive phenotype.

390  
391 *Assessment 1* will be a battery of cognitive tests currently used in clinic for the diagnosis of  
392 cognitive disorders probing working memory, attention, cognitive speed and executive  
393 function, representing domains primarily affected after CV19 infection.  
394 Specifically, assessment 1 includes:

- 395 • The Repeatable Battery for the Assessment of Neuropsychological Tests (RBANS)
- 396 • The Delis-Kaplan Executive Function System: The Trail Making Test (Condition 2:  
397 Number Sequencing & Condition 4: Number-Letter Switching)
- 398 • The Delis-Kaplan Executive Function System: Colour-Word Interference
- 399 • The Delis-Kaplan Executive Function System: Phonemic Fluency
- 400 • Wechsler Adult Intelligence Scale III: Digit Span
- 401 • Test of Premorbid Functioning (TOPF)

402 *Assessment 2* will involve the use of an online battery of cognitive tests. The first set of tests  
403 were designed in-house by [name] of the UCL Institute of Cognitive  
404 Neuroscience, and developed on Gorilla, <https://gorilla.sc/>. These tests probe speed of  
405 information processing, executive function and attention and are used in CICERO given  
406 these are the cognitive domains most commonly reported by patients as being affected in  
407 long Covid. The second online cognitive test is the 4 Mountains Test (4MT). It is a brief  
408 assessment of allocentric spatial memory, representing a key function of the hippocampus.  
409 These tests are used for research purposes only, not as clinical tools.

410  
411 *Assessment 3* will involve use of the Neotiv suite of app-based cognitive  
412 tests <https://www.neotiv.com/en>. These tests probe several aspects of episodic memory,  
413 representing different processes and functions of the hippocampus and entorhinal cortex  
414 (pattern completion, scene recognition and mnemonic discrimination) that are not adequately  
415 covered with traditional cognitive tests. These additional tests are applied to reflect i)  
416 emerging evidence that the entorhinal cortex and hippocampus are particularly vulnerable to  
417 direct viral infiltration, ii) recent work showing entorhinal-hippocampal dysfunction in people  
418 with long Covid in the absence of any subjective reporting of impairment of episodic  
419 memory.

420

*Sub-study - UK normative data for Neotiv*

There will be a substudy which will recruit 20 female, 20 male healthy participants (N=40) matching the demographic characteristics of the CICERO study. At present, the data for Neotiv has been normed in a German population. This substudy will therefore allow for the collection of UK specific normative data relevant to the CICERO sample. Healthy age-matched controls for the neotiv sub-study will be recruited via the UCL participant databases. We also intend to recruit family members of participants involved in Stage 1 and Stage 2 where eligible, as well as participants from databases associated with our collaborating research sites. Recruiting from a variety of sources will ensure access to the relevant age group and an ethnically diverse population. Testing will take place at University Hospitals Sussex NHS Trust and UCL.

*Sub-study - Normative data for 4 Mountains Test*

*The 4 Mountains Test (4MT) is a short computerised test of spatial memory. It is included as part of the cognitive assessment detailed above.* At present, there is no normative data for the 4MT. This substudy will therefore allow for the collection of UK specific normative data relevant to the CICERO sample. This substudy intends to recruit 25 female, 25 male healthy participants (N=50) matching the demographic characteristics of the CICERO study. Healthy age-matched controls for the 4MT sub-study will be recruited via the UCL participant databases. We also intend to recruit family members of participants involved in Stage 1 and Stage 2 where eligible, as well as participants from databases associated with our collaborating research sites. Recruiting from a variety of sources will ensure access to the relevant age group and an ethnically diverse population. Testing will take place at University Hospitals Sussex NHS Trust and UCL.

*Sub-study – Healthy Controls*

This sub-study encompasses the assessments from both the Neotiv and 4 Mountains Test sub-studies, while incorporating additional cognitive tests. It aims to gather UK-specific normative data pertinent to the CICERO sample by integrating the assessments conducted in the preceding sub-studies. This substudy intends to recruit 25 female, 25 male healthy participants (N=50) matching the demographic characteristics of the CICERO study.

Participants will complete the 4 Mountains Test (4MT), which is a short computerised test of spatial memory. They will also complete a selection of cognitive tests designed in-house by [name] of the UCL Institute of Cognitive Neuroscience, and developed on Gorilla, <https://gorilla.sc/>. Some participants will be invited to complete the cognitive assessment on 'neotivTrials' app.

Healthy age-matched controls will be recruited via UCL participant databases. We also intend to recruit family members of participants involved in Stage 1 and Stage 2 where eligible, as well as participants from databases associated with our collaborating research sites. Recruiting from a variety of sources will ensure access to the relevant age group and an ethnically diverse population. Testing will take place at University Hospitals Sussex NHS Trust and UCL.

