#### Data collection

Participants will give consent and complete case report forms (CRFs), including demographic information and questionnaires, via a secure REDcap weblink which will save data directly to UCL's data safe haven. In the event that participants are not able to complete the electronic consent and CRF, they will be able to attend clinic to complete a paper-based consent form and CRF. Cognitive assessment 1 and 2 will be completed in clinic, and cognitive assessment 3 will be completed remotely.

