## 12 FUNDING AND SUPPLY OF EQUIPMENT

The study is funded by a competitively awarded research grant to [name] from the National Institute for Health Research, as part of an open call for studies into Long COVID in non-hospitalised individuals. UCL will administer the grant and has a collaboration agreement with the University of Magdeburg, Germany, for usage of their Neotiv app for remote testing of cognitive function. The research grant also funds researchers at the other study sites (University of Bangor, University Hospitals Southampton NHS Trust, Greater Manchester Mental Health NHS Foundation Trust).

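### As written, healthy controls take the Neotiv tests on site while CICERO participants take them remotely, so a comparison of participants with the UK norms would mix test setting with long Covid

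*Combined protocol and SAP*

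**What the plan says.** Protocol section 5.2.1 defines cognitive assessment 3 as Neotiv: it "will involve use of the Neotiv suite of app-based cognitive" tests. Under the Data collection heading that follows, the settings are split: "Cognitive assessment 1 and 2 will be completed in clinic, and cognitive assessment 3 will be completed remotely". Section 12 describes the agreement that supplies the app as being for "usage of their Neotiv app for remote testing of cognitive function".

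The sub-study on UK normative data for Neotiv (section 5.2.1) is justified by the fact that the existing norms are German: "This substudy will therefore allow for the collection of UK specific normative data relevant to the CICERO sample". Its sample is given as follows: "There will be a substudy which will recruit 20 female, 20 male healthy participants (N=40) matching the demographic characteristics of the CICERO study". On matching and source it says: "Healthy age-matched controls for the neotiv sub-study will be recruited via the UCL participant databases". On place it says: "Testing will take place at University Hospitals Sussex NHS Trust and UCL".

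The later Healthy Controls sub-study (N=50) has controls complete the 4 Mountains Test and the Gorilla tests. It then adds: "Some participants will be invited to complete the cognitive assessment on" the neotivTrials app. It ends with the same sentence on place and makes no exception for the app.

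**The concern.** Norms are useful only if they are collected under the conditions in which they will be applied. Supervision, distraction, the device and help with the app may all differ between a hospital or university room and the participant's home. If all controls are tested in one setting and all participants in the other, setting and group are the same variable. Matching on demographics does not separate them, and neither does a larger sample.

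What is at stake is the interpretation of Neotiv in Workstream 1. The tests were added because they probe hippocampal and entorhinal memory processes that the traditional battery covers poorly. A setting effect in one direction would look like a memory deficit; in the other it would hide one. The sub-study would remove one mismatch (German norms) and introduce another.

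**Working it through.** **Reading the text.**

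| Test | CICERO participants | Healthy controls |
|---|---|---|
| Gorilla, 4 Mountains (assessment 2) | in clinic | Sussex and UCL |
| Neotiv (assessment 3) | remote | Sussex and UCL, as written |

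Only Neotiv is misaligned. No section says that a control takes Neotiv remotely or that a participant takes it on site. The in-clinic fallback under Data collection covers only the consent form and the case report form. The Workstream 1 models (section 5.2.1, Data analysis) adjust for demographic factors. No setting covariate, bridging subset or equivalence check is described.

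**Illustrating the size.** The protocol gives no calculation for the 40 controls, so there is no stated figure to reproduce.

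Inputs from the protocol: 80 Workstream 1 participants (section 5.1.1) and 40 Neotiv controls (section 5.2.1).

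Assumptions:
- a pure shift in mean of *d* SD due to setting, with equal spread in both groups and no true effect of illness;
- *d* = 0.2, 0.3 or 0.5, because the documents give no value;
- a two-sided 5% comparison of means, and a cut-off 1 SD below the control mean with that mean and SD taken as known. The protocol specifies neither analysis for Neotiv; both only illustrate.

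1. Standard error of the difference, in SD units: √(1/80 + 1/40) = √0.0375 = 0.194.
2. Probability of a significant difference from setting alone: Φ(d/SE − 1.96) + Φ(−d/SE − 1.96). For *d* = 0.2, d/SE = 1.033, giving Φ(−0.927) + Φ(−2.993) = 0.178.
3. Share of participants below the cut-off: Φ(−1 + d) if remote scores are lower, Φ(−1 − d) if they are higher.

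| *d* (SD) | Significant difference | Below −1 SD, remote lower | Below −1 SD, remote higher |
|---|---|---|---|
| 0 | 5% | 15.9% | 15.9% |
| 0.2 | 17.8% | 21.2% | 11.5% |
| 0.3 | 34.1% | 24.2% | 9.7% |
| 0.5 | 73.3% | 30.9% | 6.7% |

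The second column applies to a shift in either direction. A non-central *t* calculation gives 17.6%, 33.6% and 72.6%, which is the same after rounding.

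**The case against.** The strongest reply is that the sentence on place may be boilerplate. It appears word for word in three sub-studies, including the 4 Mountains one, where on-site testing is what one would expect. Section 12 describes the app as a remote tool. The Data collection paragraph comes after the control sub-studies and does not limit its remote statement to patients, so it can be read as covering controls. The Healthy Controls sub-study also mentions the app separately from the tests that controls will complete. This stands: controls may in practice have used the app at home. A reader might infer that every control was tested on site and that the confounding is complete. The documents do not establish that. If controls did test remotely, the sub-study text is wrong and still needs correcting.

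The second reply is that little in the specified analysis depends on these norms. This also largely stands. The Workstream 1 models concern relationships within the cross-sectional dataset, and a constant shift in the norms leaves associations among participants unchanged. No section specifies a test of participants against controls on Neotiv, or a 1 SD cut-off for it. The only 1 SD rule (SAP section 3.4) governs Workstream 2 eligibility, and its domains do not name Neotiv.

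A reader might also infer that biased norms would misdirect the rehabilitation programme, because sections 2 and 4.2 build it on the domains found most affected in Workstream 1. The documents do not say that Neotiv norms decide those domains, and the in-clinic battery also covers immediate and delayed memory.

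What remains is the sub-study's own stated purpose, which is to supply norms for the CICERO sample. Any use of the norms for that purpose compares remote scores with scores that, as written, were obtained on site.

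**Conclusion.** The point holds in a limited form. The text places control testing for Neotiv on site and participant testing at a distance, and provides nothing to separate setting from illness. If that text was followed, any reading of participants against these norms is confounded by setting.

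The size is unknown. The percentages above are conditional on assumed shifts of 0.2 to 0.5 SD and on analyses that the protocol does not specify. The direction is unknown too, so a false deficit and a masked deficit are both possible.

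The reach is Workstream 1 only. The randomised comparison is not affected, because both arms complete assessment 3 under the same stated conditions. The 4 Mountains and Gorilla norms are not affected, because both groups take those tests on site.

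**What to change.** Reconcile the two sub-study descriptions in section 5.2.1 with the Data collection paragraph. State that controls complete Neotiv remotely, with the same instructions, device rule and schedule as participants, and that only the 4 Mountains and Gorilla tests are done on site.

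The current protocol (v1.13) is dated 20/12/2024 and the study was expected to end in February 2025, so many controls may already have been tested. For them:
- record the setting of every Neotiv session;
- offer a remote session to any control tested on site, which also gives a bridging subset tested both ways. The remote session would always come second, so the difference would also contain any practice effect;
- do not pool the two settings without that check;
- where it cannot be done, report the setting difference as a limitation of the norms.

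The cost is a change of wording, less supervision of controls during the app tests, and some re-contact. If controls were in fact tested remotely, correcting the text and recording the setting is enough.

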#### *Sub-study – Cognitive rehabilitation workshop for control group participants*

Control group participants will be invited to participate in an online workshop with a focus group outlining the strategies used in neuropsychological rehabilitation of cognitive impairment in long Covid ("cognitive Covid"). The workshop has dual objectives: firstly is to explore the experiences of individuals living with cognitive Covid and their coping mechanisms. Secondly, to provide an educational workshop on the neuropsychological strategies used in cognitive rehabilitation that may be used to cope with cognitive difficulties associated with long Covid syndrome. The session will be recorded for analysis purposes and direct quotations from participants (de-identified) may be used in publications. The expected duration of the workshop is 1.5 hours in a single session. Before the start of the workshop, we will give participants the option to keep their cameras off for the duration of the workshop, if they do not wish to be video recorded. We will video-record the workshop with an automatic transcript on MS Teams. Within 72 hours after the workshop, two research assistants will compare the automatic transcript against the video recording. Afterwards, they will upload the transcript to Data Safe Haven (DSH), and the video recording will be deleted.

